### 4.2 Output variables

We expect to model all secondary outcome variables, except survival, recurrence, new primary/secondary cancer, re-admission rates, re-operation rates, costs and resource use, and adverse events. The final decision will depend on the available data. For example, if the counts for conversion to open surgery rates are very low, we will not model this outcome.

Therefore, we plan on analysing:

- Morbidity (five variables not including 2iii survival)
- Operative outcomes (seven variables not including re-operation and re-admission rates)
- Hospital stay (two variables)
- Anthropometry (two variables)
- Fitness (one variable)
- Health-related quality of life (HRQoL) (three variables)

That's twenty variables equating to at least 20 models, as some of those variables will be further subdivided (eg HRQoL variable "EQ-5D-5L" has two subdivisions, index and VAS).

#### 4.3 Model selection for a given outcome variable

*See Appendix “Use Of The Word “Linear” In Linear Models” for an explanation of the use of the word “linear” even if the underlying curve is a higher polynomial*

The output variables may be continuous or categorical and the input variables may be categorical or continuous. This would imply a logistic model (logistic regression or discriminant analysis) or a linear model (linear regression or ANOVA or ANCOVA or mixed) or a generalized model (GLM) approach. As GLMs are the most capable, we will use GLMs for our models where possible.

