## 4. USE OF MODELS

### 4.1 Input variables

The SAP states that the mean and 95% confidence intervals for the secondary outcome variables will be estimated with adjusted regression models. Those adjustments will be our four input variables, specifically:

- treatment group. There are two treatment groups, the control and the intervention.
- baseline value (where applicable)
- time point (where applicable)
- stratification variables. The two stratification variables are performance status (0 vs 1-2) and age at diagnosis ( $\leq$ / $\geq$ 70 years). These will be combined into one [1][2].

The extension from regression models to mixed models was not explicitly stated but is assumed. Such models will have fixed effects and may be further extended to include a random effect and/or an interaction. Details of those models include:

- The fixed effects are the adjustments
- The random effect is the participant/study ID
- The interaction is multiplicative. For example, an interaction between the treatment group and the time point (both of which are fixed) will be considered.

In models with interaction terms, the treatment effect will be the interaction term. In models without an interaction term, the treatment effect will be the treatment group.

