|                                        | xii. Radiologically -defined anastomotic leaks                | ditto                                                                | Binary                          | Binomial      |            |
|                                        | xiii. Length of time in intensive care unit                   | ditto                                                                | Continuous                      | See lookup    |            |
|                                        | xiii. Length of time in high dependency unit                  | ditto                                                                | Continuous                      | See lookup    |            |
|                                        | xiv. Re-operation rates                                       | xiv-xv: 30-days post-op and 3 years                                  | N/A: not model                  |               |            |
|                                        | xv. Re-admission rates                                        | ditto                                                                | N/A: not model                  |               |            |
|                                        | 5. Hospital stay                                              | xvi. Length of hospital stay (fitness to discharge)                  | xvi: Discharge                  | Time-to-event | See lookup |
|                                        |                                                               | xvii. Days alive and out of hospital                                 | xvii: 30-days post- operatively | Time-to-event | See lookup |
| 6. Anthropometry                       | xviii. Weight                                                 | xviii-xix: Baseline, pre-operative assessment 4, and 30 days post-op | Continuous                      | See lookup    |            |
|                                        | xix. Fat-free mass (absolute kg)                              | ditto                                                                | Continuous                      | See lookup    |            |
|                                        | xix. Fat-free mass (relative %)                               | ditto                                                                | Continuous                      | See lookup    |            |

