## 15.4 Sensitivity Analyses

Sensitivity analyses will be done on at least the following:

- **Per-protocol analysis.** The per-protocol analysis will repeat the above models using the per protocol population as defined in section 3.
- **Stratification factors.** The two stratification factors are performance status (“0” vs “1-2”) and age at diagnosis (“< 70 years” and “ $\geq$ 70 years”). For sensitivity analysis we will do the following:
  - Repeat the models with an interaction term between age at diagnosis (“< 70 years” and “ $\geq$ 70 years”) and treatment. This will be expanded to “...and treatment and time” if time is an input variable, see below.
  - Repeat the models with an interaction term between performance status (“0” vs “1-2”) and treatment. This will be expanded to “...and treatment and time” if time is an input variable, see below.
  - Models measuring the state at one timepoint (eg discharge) or the state change between two timepoints will not need a time variable. Models measuring the state at two or more timepoints (eg baseline vs admission vs 30-days post-op) will need a time variable. In such cases, the interaction above will include the time variable. The paper at [7] is an example of this.
- **Other.** Other sensitivity analyses may be conducted if deemed necessary by the Trial Statistician.

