### 22.1 GLMs

| #  | Variable Type                 | Distribution                              | Link Fn   | Example Stata Code †††                      |
|----|-------------------------------|-------------------------------------------|-----------|--------------------------------------------------------|
| 1  | Continuous (Normal)           | Gaussian                                  | Identity  | glm depvar indepvars, family(gaussian) link(identity)  |
| 2  | Continuous (SPC) † | Inverse Gaussian                          | Power -2  | glm depvar indepvars, family(igaussian) link(power -2) |
| 3  | Binary                        | Binomial (multiple) or Bernoulli (single) | Logit     | glm depvar indepvars, family(binomial) link(logit)     |
| 4  | Count/Rate (Poisson)          | Poisson                                   | Log       | glm depvar indepvars, family(poisson) link(log)        |
| 5  | Count/Rate (NB)               | Negative binomial                         | Log       | glm depvar indepvars, family(nbinomial) link(log)      |
| 6  | Continuous (SPC) † | Gamma                                     | Power -1  | glm depvar indepvars, family(gamma) link(power -1)     |
| 6  | Continuous (Time)             | Gamma?                                    | Power -1? | glm depvar indepvars, family(gamma) link(power -1)     |
| 99 | Time-to-event                 | Exponential ††                 | Log       | glm depvar indepvars, family(exponential) link(log)    |

† SPC = Skewed positive continuous variable.

†† Not available in Stata. Code shown is synthetic. GLMs in this case would require another language

††† For a full list of families, link functions in Stata and their valid combinations, please see Stata help. Note that “inverse” is the same as “power -1”, “inverse squared” is the same as “power -2”, and so on

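### For outcomes with two post-baseline visits, the SAP supplement contradicts itself on whether within-patient correlation is modelled; if its GLM rule is applied to stacked visits, the secondary 95% CIs are miscalibrated.

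*Combined protocol and SAP*

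**What the plan says.** All places below are in the supplement to the SAP on secondary outcomes.

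- **Visits (section 5, table of secondary outcomes).** Weight and fat-free mass are listed at "xviii-xix: Baseline, pre-operative assessment 4, and 30 days post-op". EQ-5D-5L and HADS are listed at baseline, pre-operative assessment 3 and 30 days. The model for all of them is left to the lookup tables.
- **Mixed models (4.1).** "The extension from regression models to mixed models was not explicitly stated but is assumed". The grouping level is named: "The random effect is the participant/study ID". But the effect is permissive: models "may be further extended to include a random effect and/or an interaction". Where an interaction is fitted, the interaction term is taken as the treatment effect.
- **Model choice (4.3).** Mixed models appear as one linear-model option among several, and the rule that follows is "As GLMs are the most capable, we will use GLMs for our models where possible".
- **Code (22.1, 22.2).** The row for a normally distributed continuous outcome begins "glm depvar indepvars, family(gaussian) link(identity". No row in either table has a participant term, a clustered standard error or a repeated-measures covariance.
- **Stacked visits (15.4).** "Models measuring the state at two or more timepoints (eg baseline vs admission vs 30-days post-op) will need a time variable". Within-patient correlation is not mentioned there.
- **Worked example (Appendix 20.3).** For weight, the random intercept is for the two arms, arm is not among the fixed effects, and there are 72 outcome values although timepoint is a predictor.
- **Missing data (15.1).** Imputation is declined, partly on the ground that mixed models usually do not need it.

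**The concern.** A Gaussian GLM can always be fitted to weight, fat-free mass, EQ-5D-5L or HADS. Read literally, the rule in 4.3 and the code in 22.1 therefore lead to a model that treats one patient's two visits as two patients. Appendix 20.3 does not prevent this, because an arm-level intercept does not capture correlation within a patient. Section 4.1 points the other way without requiring it. Two competent statisticians could follow this text and report different intervals from the same data.

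No p-values will be reported, so the 95% CIs are the only statement of between-arm uncertainty for these outcomes, and they are likely to inform the design of a definitive trial. The reason 15.1 gives for not imputing also weakens if the model fitted is not a mixed model.

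**Working it through.** **The plan's own figures.** The documents give no standard error, interval width or within-patient correlation for these outcomes, so there is nothing of that kind to reproduce. The collective power in SAP 3.3 (0.93 × 0.92 × 0.99 = 0.847, stated as 85%) concerns the progression criteria and does not depend on this point.

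**Set side by side**

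| Place | Participant-level correlation? |
|---|---|
| 4.1 | Assumed and named, but optional |
| 4.3 | GLM preferred; mixed is one alternative |
| 22.1, 22.2 | Absent from every row |
| 15.1 | Mixed models presumed |
| 20.3 | Random intercept on arm; 72 rows, where 72 patients × 2 post-baseline visits would be 144 |

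**Inputs for the size**
- 36 patients per arm (protocol 11.3, SAP 3.3).
- Two post-baseline visits, baseline as covariate (supplement 4.1 and 5).
- Raw correlation rho between any two visits: not in the documents. Assumed exchangeable, range 0.3 to 0.9.

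**Formulas.** After adjustment for baseline, the two visits have residual correlation

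r = (rho − rho²)/(1 − rho²) = rho/(1 + rho).

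With two rows per patient treated as independent:
- pooled treatment term: true SE / reported SE = sqrt(1 + r), so the CI is too narrow;
- treatment-by-time term: reported SE / true SE = 1/sqrt(1 − r), so the CI is too wide.

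For rho = 0.5: r = 0.5/1.5 = 0.333. Pooled term: sqrt(1.333) = 1.155 and 1.96/1.155 = 1.697, giving 91.0% coverage. Interaction: 1/sqrt(0.667) = 1.225 and 1.96 × 1.225 = 2.40, giving 98.4% coverage.

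**Results** (simulation: 4,000 trials per rho, ordinary least squares on 144 rows)

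| rho | r | Pooled: coverage, formula / simulated | Treatment-by-time: coverage, formula / simulated | Treatment-by-time: reported/true SE, formula |
|---|---|---|---|---|
| 0.3 | 0.231 | 92.3% / 92.7% | 97.5% / 97.5% | 1.14 |
| 0.5 | 0.333 | 91.0% / 90.7% | 98.4% / 98.4% | 1.22 |
| 0.7 | 0.412 | 90.1% / 89.8% | 98.9% / 98.8% | 1.30 |
| 0.9 | 0.474 | 89.4% / 89.6% | 99.3% / 99.2% | 1.38 |

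In the simulations, a participant-level analysis of the same data covered 94.4% to 95.5% throughout. Mean CI widths, independent rows against participant level, in SD units:
- pooled term: 0.63 against 0.70 at rho 0.3, and 0.29 against 0.35 at rho 0.9;
- treatment-by-time: 1.25 against 1.11, and 0.57 against 0.42.

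**If baseline is a response row.** Without the baseline covariate, treatment-by-time SEs are inflated by 1/sqrt(1 − rho): 1.41 at rho 0.5 and 3.16 at rho 0.9. With the covariate kept, simulated reported/true SE is only about 0.92 to 1.16 over rho 0.3 to 0.9 (two or three rows per patient).

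**The case against.** The strongest reply is that mixed modelling was clearly intended. Section 4.1 assumes it and names the participant, 15.1 relies on it, and Appendix 20 sets out the theory. The permissive wording has an innocent explanation: 4.1 covers about twenty outcomes, most with one value per patient, for which a compulsory random effect would be wrong. The lookup code is headed as example code and serves mainly to choose a distribution and link. Section 15.4 is about sensitivity analyses and also allows single-timepoint and change-score models. Several of these outcomes are to be displayed by timepoint, which fits a separate ANCOVA at each visit with one row per patient.

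Most of this stands. A reader might infer that the plan specifies an independence analysis and that the reported CIs will be wrong. The documents do not support that: they are contradictory, and the error is conditional on visits being stacked without a participant term. A reader might also infer very wide weight intervals from the 1/sqrt(1 − rho) factor. That needs baseline as a response row and the baseline covariate dropped, whereas SAP 3.7.2 and supplement 4.1 adjust for baseline where applicable, which it is for weight.

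The reply does not remove the contradiction. An innocent reason for optional wording is not a rule for when the effect is required, and the one worked mixed model uses the wrong grouping level.

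**Conclusion.** The point holds as an internal contradiction that should be resolved before analysis. It covers weight, fat-free mass, EQ-5D-5L index and VAS, and HADS anxiety and depression. Sit-to-stand has one post-baseline visit and is affected only if baseline is a response row. Morbidity is collapsed to one value per patient, and the CR29 items are descriptive.

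If the GLM rule or the Appendix 20.3 example is applied to stacked visits, with baseline as covariate, nominal 95% CIs cover about 93% down to 90% for a treatment effect pooled over two post-baseline visits. For treatment-by-time they cover about 97.5% to 99%, with SEs about 1.1 to 1.4 times too large. The direction thus depends on which term is read as the treatment effect. These sizes rest on an assumed exchangeable correlation of 0.3 to 0.9.

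The consequence is moderate. The intervals are secondary, nominal and descriptive, and no progression decision depends on them.

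**What to change.** - **4.1:** state that every model with two or more response rows per participant will include a participant random intercept, or an unstructured within-participant covariance, or participant-clustered standard errors. Say for each outcome whether visits are stacked or analysed separately, and whether baseline is a covariate or a response row.
- **4.3, 22.1 and 22.2:** limit the plain glm, reg and logit rows to outcomes with one row per participant, and add mixed and meglm rows grouped by participant ID.
- **Appendix 20.3:** make arm a fixed effect and participant the random effect, and set the number of rows to patients × visits (144 for two post-baseline visits).

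The cost is a revision of the supplement's wording, with no new data. The models become slightly more complex and need convergence checks.

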## 5. LIST OF SECONDARY OUTCOMES

**Table: secondary outcomes**

| Objectives                             | Outcome Measures                                              | Timepoint(s)                                                         | Type                            | Distribution  |            |
|----------------------------------------|---------------------------------------------------------------|----------------------------------------------------------------------|---------------------------------|---------------|------------|
| To report between-group differences in |                                                               |                                                                      |                                 |               |            |
| 2. Morbidity                           | i. Any morbidity                                              | i.-ii. Discharge and 30-days post-op                                 | Binary                          | Binomial      |            |
|                                        | ii. Morbidity by grade (I, II, IIIa, IIIb, IVa, IVb)          | ditto                                                                | Binary                          | Binomial      |            |
|                                        | iii. Survival (grade V)                                       | iii: Discharge, 30-days post-op, 3 yrs                               | N/A: not model                  |               |            |
|                                        | iv Morbidity by highest grade                                 | i.-ii. Discharge and 30-days post-op                                 | Binary                          | Binomial      |            |
|                                        | v. Number of people with no morbidity                         | iii: Discharge, 30-days post-op, 3 yrs                               | Binary                          | Binomial      |            |
|                                        | vi. Morbidity by type (e.g., arrythmia, wound infection, etc) | i.-ii. Discharge and 30-days post-op                                 | Binary                          | Binomial      |            |
| 3. Oncological outcomes                | iv. Resection margins (involved Y/N)                          | iv. Discharge                                                        | Binary                          | Binomial      |            |
|                                        | v. Recurrence                                                 | v-vi: 3 years                                                        | N/A: not model                  |               |            |
|                                        | vi. New primary/ secondary cancer                             | ditto                                                                | N/A: not model                  |               |            |
| 4. Operative outcomes                  | vii. Intraoperative blood loss                                |                                                                      |                                 |               |            |
|                                        | Count/rate (transfused Y/N)                                   | vii-ix: Discharge                                                    | Binary                          | Binomial      |            |
|                                        | units transfused (including untransfused)                     | ditto                                                                | Continuous                      | See lookup    |            |
|                                        | viii. Operative time                                          | ditto                                                                | Continuous                      | See lookup    |            |
|                                        | ix. Conversion to open surgery                                | ditto                                                                | Binary                          | Binomial      |            |
|                                        | x. Surgical site infection                                    | x-xiii: Discharge and 30-days post-op                                | Binary                          | Binomial      |            |
|                                        | xi. Stoma rates                                               | ditto                                                                | Binary                          | Binomial      |            |
|                                        | xi. Stoma complications                                       | ditto                                                                | Binary                          | Binomial      |            |
|                                        | xii. Radiologically -defined anastomotic leaks                | ditto                                                                | Binary                          | Binomial      |            |
|                                        | xiii. Length of time in intensive care unit                   | ditto                                                                | Continuous                      | See lookup    |            |
|                                        | xiii. Length of time in high dependency unit                  | ditto                                                                | Continuous                      | See lookup    |            |
|                                        | xiv. Re-operation rates                                       | xiv-xv: 30-days post-op and 3 years                                  | N/A: not model                  |               |            |
|                                        | xv. Re-admission rates                                        | ditto                                                                | N/A: not model                  |               |            |
|                                        | 5. Hospital stay                                              | xvi. Length of hospital stay (fitness to discharge)                  | xvi: Discharge                  | Time-to-event | See lookup |
|                                        |                                                               | xvii. Days alive and out of hospital                                 | xvii: 30-days post- operatively | Time-to-event | See lookup |
| 6. Anthropometry                       | xviii. Weight                                                 | xviii-xix: Baseline, pre-operative assessment 4, and 30 days post-op | Continuous                      | See lookup    |            |
|                                        | xix. Fat-free mass (absolute kg)                              | ditto                                                                | Continuous                      | See lookup    |            |
|                                        | xix. Fat-free mass (relative %)                               | ditto                                                                | Continuous                      | See lookup    |            |
| 7. Fitness                             | xx. Time for sit-to-stand test                                | xx: Baseline, 30 days post-op                                        | Continuous                      | See lookup    |            |
| 8. HRQoL                               | xxi. EQ-5D-5L (Index score)                                   | xxi-xxii: Baseline, pre-operative assessment 3 and 30 days post-op   | Continuous                      | See lookup    |            |
|                                        | xxi. EQ-5D-5L (VAS)                                           | ditto                                                                | Continuous                      | See lookup    |            |
|                                        | xxii. HADS (anxiety) continuous                               | ditto                                                                | Continuous                      | See lookup    |            |
|                                        | xxii. HADS (depression) continuous                            | ditto                                                                | Continuous                      | See lookup    |            |
|                                        | xxiii. EORTC-QLQ-CR29                                         |                                                                      |                                 |               |            |
|                                        | 29 individual items                                           | ditto                                                                | N/A: not model                  |               |            |
| 9. Costs & resource use                | N/A - dealt with by health economics                          |                                                                      |                                 |               |            |
| 10. Adverse events                     | xxvii. Adverse events (excluding morbidity i-vi)              | xxvii: Baseline, pre-operative assessment and 30 days post-op        | N/A: not model                  |               |            |

Details of each variable are provided below.

